#### Multivariable analyses

We will apply ICH-E9 guidelines for statistical analysis and the CONSORT statement for reporting of findings for clinical trials [31, 34]. For multivariable analyses, linear regression or logistic regression will be used to adjust for baseline characteristics that do not appear to be balanced upon inspection or show moderate to large standardized effect sizes. Covariates that do not meaningfully modify estimates of treatment effect or otherwise contribute to clinical interpretation may be removed from the final model.

In multivariable models, we will assess for heterogeneity of treatment effects by including interaction terms (specifically, age, gender, and race/ethnicity, insurance, education, and health literacy) with treatment group [35]. In view of our limited sample size to detect significant interaction terms, we will consider any interaction term as worthy of further evaluation if significance testing achieves a critical test level of 0.15.

Our primary analyses will proceed via an intention-to-treat approach, as some cross-over is expected. All measures of treatment effects (e.g., odds ratios, difference in means or proportions) as well as estimates of group specific effects (e.g., means and proportions) will be reported with 95% confidence intervals. However, patients with exclusion criteria that manifest post-randomization will NOT be included (ex. pregnancy diagnosed in the ED).

### Interim analyses {21b}

The first interim analysis, which will occur after 50 patients are enrolled, will only consider feasibility and fidelity of the protocol (i.e., whether recruitment and retention goals are met, whether the protocol is acceptable to clinicians, and whether the protocol is being administered as planned). There will be no planned assessment of efficacy outcomes at this interim analysis. As such, there will be no adjustment to the *p* value for this interim analysis.

At the second interim analysis (approximately 100 patients evaluable for efficacy), we will evaluate the sample to determine whether further enrichment of the sample is required (e.g., further refinement of inclusion/exclusion criteria, such changing the maximum age or excluding patients with a history of ureterolithiasis). We will assess efficacy as this interim analysis, and therefore will adjust the critical test level accordingly. Using the O’Brien-Fleming approach to the alpha spending function, one evaluable interim look at approximately 50% of the sample, the critical test levels for early termination for efficacy will be *p* ≤ 0.003 and *p* ≤ 0.047, for a two-sided test [36, 37]. That is, if at the first evaluable interim analysis the difference between study groups in both primary outcomes achieves a significance level of *p* ≤ 0.003, the study will stop. The final significance test will be conducted at *p* ≤ 0.047, rather than *p* ≤ 0.05.

Initial data analysis will describe the distribution of all outcomes by treatment group. Continuous measures will be reported using means, standard deviations, medians, and percentiles. Categorical measures will be reported using frequencies and percentages. Rather than testing baseline covariate imbalance, stratified analyses will be conducted for baseline covariates that are known to be strongly associated with outcomes, as well as those that show imbalance on inspection [38].

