### Sample size {14}

As per Fig. 3, three discrete analysis times are planned.

Our sample size for phase I (until interim analysis 1) is based on the expert recommendation that at least 50 subjects be included to examine the pragmatics of recruitment [30].

For the endpoint of reduction in the use of CT scans, assuming a base proportion of 80% (currently, the usage rate for kidney stones), a sample of 200 patients (100 patients per group) will provide 87% power to detect a reduction of CT use to 60%, as significant at a *p* value of 0.047 (adjusted to account for the interim efficacy analysis—see explanation below). A final sample size of 200 is large enough to account for a loss of 10% and still provides about 80% power to detect the hypothesized difference. If lost to follow-up rates are higher, a sample size of 250 will be used (125 patients per group).

For the endpoint of knowledge, we hypothesize that an improvement of 2 points (of 10) is clinically significant. If the decision aid improves knowledge from 6/10 to 8/10, we will be powered at 0.80 to detect this with a total of 70 participants.

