### Data management {19}

All data collected will be stored using REDCap (Research Electronic Data Capture) hosted by the Tufts Clinical and Translational Science Institute. Electronic capture data point fields will include range limits to protect against accidental entry of impossible data points. Direct data entry at the time of collection will be utilized when possible, but paper forms will be available in the event of connectivity issues. Paper forms will be managed via standard operating procedures, they will be transported directly to research offices after use and stored in locked cabinets prior to data entry. Data entry will occur as close to data acquisition as logistically possible. Data management will be performed by trained research staff under the supervision of the PI. The PI will not have access to the randomization dataset while the trial is ongoing, other than at pre-specified points.

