### Composition of the data monitoring committee, its role and reporting structure {21a}

A Data Safety Monitoring Plan (DSMP) is in place and included separately (Supplementary Material 6). As this study is minimal risk, it does not require a full independent DSMB. However, the DSMP utilizes external physician reviewers for all Serious Adverse Events and clearly delineates definitions of adverse events and stopping rules. The study will be paused and independently reviewed if 3 “Serious, Moderate/Severe” SAEs determined to be “probably related” are reported. Specific details are listed in the DSMP.

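### Eligibility may be changed at the same interim look that tests efficacy by arm, and nothing separates the two decisions, so type I error control is not assured and the target population is not fixed

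*Protocol article*

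**What the plan says.** Interim analyses {21b} gives the second interim two tasks. The first concerns eligibility: "we will evaluate the sample to determine whether further enrichment of the sample is required", with examples "such changing the maximum age or excluding patients with a history of ureterolithiasis". The second is an efficacy comparison of the arms, for which the levels are adjusted by O'Brien-Fleming-type spending with a single efficacy look about halfway through: "the critical test levels for early termination for efficacy will be *p* ≤ 0.003 and *p* ≤ 0.047, for a two-sided test". Early stopping requires both primary outcomes to reach 0.003. Sample size {14} gives the same reason for the final level: "0.047 (adjusted to account for the interim efficacy analysis—see explanation below".

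On access, Data management {19} states: "The PI will not have access to the randomization dataset while the trial is ongoing, other than at pre-specified points". Sequence generation {16a} likewise closes the randomization database to the PI and statisticians only until the planned interims. On oversight, section {21a} says of the study that "it does not require a full independent DSMB"; external physicians review serious adverse events.

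The final CT comparison is a Pearson chi-square (section {20a}). The primary analyses are by intention to treat, leaving out patients whose exclusion criteria emerge after randomization (Multivariable analyses).

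**The concern.** An O'Brien-Fleming adjustment covers repeated testing of one fixed hypothesis. It does not cover choosing which population to test after looking at its results. Here the two decisions share a look and a team, and the article gives no order, no rule and no requirement that the eligibility decision be made without knowledge of arm.

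Two things are at stake. One is the final test: its error rate depends on how patients enrolled under the earlier criteria enter it, which the article does not say. The other is the meaning of the estimate. Stone history is the randomization stratum, and patients with a history receive a different form of the aid, so dropping them midway changes the question being answered.

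**Working it through.** **Inputs from the protocol.** CT use 80% v 60%; 100 per group; two-sided levels 0.003 and 0.047; one efficacy look at about 50% of the sample; 1:1 allocation.

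**1. The plan's own figures.** The critical value for 0.047 is 1.986. Under the null, SE = √(2 × 0.7 × 0.3 / 100) = 0.0648. Under the alternative, SE = √((0.16 + 0.24) / 100) = 0.0632. Power = Φ((0.20 − 1.986 × 0.0648) / 0.0632) = Φ(1.127) = 87.0%, which matches the stated 87%.

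O'Brien-Fleming-type spending at half the information gives 0.0031 and 0.0490. The stated 0.003 reproduces, and 0.047 (= 0.05 − 0.003) is slightly conservative. Total two-sided error for one outcome is 1 − P(|Z₁| < 2.968 and |Z| < 1.986), with correlation √0.5, which is 0.0480. Only 0.002 is spare for any further adaptation.

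**2. All randomized patients pooled.** With equal stages, Z = √0.5·Z₁ + √0.5·Z₂. If the aid has no effect in anyone, Z₂ is a fresh standard normal variable whoever is enrolled in stage 2, so the choice of population does not change the error rate. Simulation of the chi-square test agrees: 4.8-4.9% two-sided, about 2.4% on the favourable side. This needs fixed stage sizes. If the total were raised from 200 to 250 because the interim result was weak, pooled error would be 5.2-5.3%. The protocol ties that increase to loss to follow-up, not to the result.

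**3. What the pooled estimate describes.** Illustration, with assumed figures: half of patients have a stone history; the aid lowers CT use by 20 points in those without a history and by 0 in those with one; history patients are dropped for stage 2. The pooled arms then hold 25 of 100 patients with a history.

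- Original population: 0.5 × 20 = 10 points
- Pooled trial estimate: 0.75 × 20 = 15 points
- Retained population: 20 points

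The trial's estimate matches neither population.

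**4. Final test restricted to a population chosen from interim effects.** Assumptions not in the protocol: CT use 80% everywhere (no effect), 50 per arm per stage, four equal history-by-age cells, the best-looking candidate retained with its own stage 1 patients, all other stage 1 patients dropped, CT outcome only, and stopping on CT alone at 0.003. There were 400,000 simulated trials per row.

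| Candidate populations | Favourable-side error | Bias toward the aid |
|---|---|---|
| All patients only | 2.4% | none |
| All, or no history | 3.5% | 1.2 points |
| All, no history, or young | 4.3% | 1.9 points |
| As above, plus young with no history | 4.7% | 2.2 points |

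Two-sided error over the last three rows is only about 5.0-5.6%, because selecting favourable results removes most rejections in the other direction. The figures depend on the menu of choices: if either half of a single split may be chosen, favourable-side error is 4.3-4.5% and two-sided error 5.2-5.3%.

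**The case against.** The strongest reply is that the stated analysis is sound. Intention to treat with one chi-square implies that everyone randomized is compared, and step 2 shows no inflation there. The only exclusions the protocol describes are criteria that emerge after randomization. They do not reach a patient who was eligible when enrolled. This stands, and it is why a reader who infers that error control is lost goes further than the documents allow.

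A reader might also infer that the population will be chosen from effects by arm. The protocol does not say so. It speaks of evaluating the sample, and its fault is that it does not keep the two decisions apart. The inflation in step 4 is therefore conditional. The plan's test is also two-sided, and the two-sided rise is small.

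Finally, Fig. 3, the Data Safety Monitoring Plan and any SAP are not shown, and could hold an enrichment rule or a reporting firewall. The absence of such detail from an article is not itself a fault. What remains comes from what the article does state: an open list of eligibility changes, at an efficacy look, with PI access to allocation, and a final level justified by the efficacy look alone. Analysis oversight by the Biostatistics Core and IRB review of amendments do not keep the interim effect from those deciding eligibility.

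**Conclusion.** The point holds in this form: as written, the plan permits the population to be chosen with knowledge of interim effects, so type I error control is not assured and the target population is not fixed.

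Under the most natural reading (everyone pooled, stage sizes fixed) the test keeps about 4.8-4.9% against the null of no effect in anyone. The cost then falls on interpretation, because the estimate covers a mixture of old and new criteria that may have been chosen from the data. Under the restricted reading, the damage lies mainly in the direction that favours the aid: 3.5-4.7% instead of 2.4%, with 1.2-2.2 points of bias. Those figures rest on four equal cells, one to three added candidates, and always keeping the best-looking one. None of these is in the protocol.

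This is more than missing detail, because knowledge of the interim effect cannot be withdrawn once the look has taken place.

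**What to change.** In Interim analyses {21b}, state that:

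- any enrichment decision uses only pooled data blind to arm (for example overall CT rate, and recruitment and retention by age and stone history), and is made and recorded before the efficacy comparison is opened;
- the final test at 0.047 includes all randomized patients from both stages under intention to treat, with results by stage and by stone history reported alongside;
- a Biostatistics Core statistician runs the efficacy look, and the PI receives only the message to stop or to continue.

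Bring the access statements in {16a} and {19} into line with the last item. The levels 0.003 and 0.047 can then stand, and no extra patients are needed. The cost is wording, separation of roles, and less freedom to choose the population from interim effects.

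Only if enrichment on unblinded effects is wanted is more machinery needed: options fixed in advance, an inverse-normal combination of the two stages with fixed weights, and closed testing. A simulated version with one 50/50 split had a one-sided family-wise error of 0.021 (limit 0.025), against about 0.045 for the unadjusted test in the selected population.

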### Methods for additional analyses (e.g., subgroup analyses) {20b}

Due to anticipated cross-over, we will also assess for contamination, as it is expected that some proportion of the usual care group will have elements of a Shared Decision-Making conversation with their clinician. Contamination will be measured via two methods: self-report by clinicians (“Did you have a SDM conversation with the patient?”) and 3rd party assessment via the OPTION-5 scale [25]. As a secondary analysis, a per-protocol analysis will examine efficacy. That is, treatment received (per-protocol) will be determined by research staff assessment, and a per-protocol analysis will be performed. Per CONSORT guidelines, this will be presented in parallel with the intention to treat analysis [39]. As SDM may be delivered in the usual care group, but without the decision aid, we expect that a per-protocol analysis may results in three distinct groups: one – randomized to usual care and did not received SDM, two – randomized to usual care and received SDM (without the decision aid), and three – randomized to SDM and received both SDM and the decision aid.

### Methods in analysis to handle protocol non-adherence and any statistical methods to handle missing data {20c}

As noted above in additional analysis, a secondary, per-protocol analysis will examine outcomes by whether or not the participant was engaged in Shared Decision-Making, as reported by clinicians and judged by study staff, regardless of whether the decision aid was used.

Missing data will be described and, if extensive, limitations will be identified in our discussion. We will compute standardized effect sizes to help determine the degree of imbalance on baseline characteristics and subsequently inform multivariable model development.

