**Fig. 3 Fig3:**
[figure not shown]
Adaptive design: interim analyses

Recruitment will be considered feasible if > 3 participants are enrolled per month and the follow-up rate is at least 70%. Acceptability will be measured by a 7-point Likert scale, and the acceptability goal will be having > 50% of clinicians reporting the decision aid to be somewhat or extremely helpful. Regarding fidelity, a 3rd party will rate conversations on pre-defined criteria for SDM (OPTION-5 scale: *observing patient involvement*) [25]. If > 50% of intervention group conversations and < 30% of usual care conversations are rated as utilizing SDM, this condition will be considered satisfied. If two of three initial goals are not met (recruitment, acceptability, and fidelity), we will pause the trial and implement appropriate changes to the protocol.

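### The plan's stated handling of missing data is description and discussion only, although two parts of the radiation primary outcome need 60-day follow-up and 70% follow-up counts as feasible

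*Protocol article*

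**What the plan says.** Section {20c} of the protocol article is the item for statistical methods for missing data. On that subject it states: "Missing data will be described and, if extensive, limitations will be identified in our discussion". Apart from that it covers the per-protocol analysis and baseline imbalance. No other section gives a rule for a missing outcome.

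Other sections bear on the point:

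- Outcomes {12} makes radiation exposure one of two primary outcomes. It is measured as CT at the ED visit and within 60 days, and as total radiation over 60 days.
- Under Multivariable analyses: "Our primary analyses will proceed via an intention-to-treat approach, as some cross-over is expected".
- Outcomes {12}, feasibility: "Recruitment will be considered feasible if > 3 participants are enrolled per month and the follow-up rate is at least 70"%. The consequence of failing is limited: "If two of three initial goals are not met (recruitment, acceptability, and fidelity), we will pause the trial".
- Sample size {14} allows for 10% loss and raises the total to 250 if loss is higher.
- Section {18a} provides for chart review of reported events and authorization to obtain outside records.
- Section {18b} has the hospital record searched for high-risk diagnoses with complications (HRDwC) in patients who cannot be reached. If none is found, or there are no data on further care, the patient counts as lost.

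**The concern.** The item meant to hold a method holds a reporting intention. The planned chi-square and t-tests use observed values, so randomised patients with unknown 60-day status would drop out by default from an analysis called intention-to-treat. Nothing planned would show whether the result survives that.

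For any CT within 60 days, the gap need not be neutral between arms. A patient scanned at the ED visit has a known status whatever happens later. Only a patient who left without a CT can become unresolved, and the trial's hypothesis is that the aid arm has more of these. The reported 60-day effect could then depend on a rule chosen after the data are seen. The larger sample of 250 addresses precision, not this.

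**Working it through.** **The plan's own figure.** The inputs from Sample size {14} are: "a sample of 200 patients (100 patients per group) will provide 87% power to detect a reduction of CT use to 60"%, from a base of 80%, at two-sided 0.047. With the pooled-variance formula:

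- Φ[(0.20 − 1.986·√(2·0.7·0.3/100)) / √((0.16 + 0.24)/100)] = 87.0%. The stated 87% reproduces.
- At 90 per group (10% loss) the same formula gives 83.3%, or 78.8% with continuity correction, so the stated figure of about 80% is fair.
- At 30% loss with every lost patient dropped, power is 72.9% with 70 per group (200 enrolled) and about 82% with 87 per group (250 enrolled). The contingency therefore does restore power.

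**Inputs for the missing-data check.**

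- CT at the ED visit: 80% usual care and 60% aid. These are the planning rates; reading them as ED-visit CT is an assumption.
- Loss L: 30% (the feasibility threshold) or 10% (the sample-size allowance), equal in both arms.
- Later-CT rate r among patients without an ED-visit CT: 25%, an assumption varied below.
- No status recovered from records, so the unresolved shares are upper figures.

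**Formulas**, with p the ED-visit CT rate:

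- True 60-day rate = p + (1 − p)·r
- Unresolved share u = (1 − p)·L
- Known CT share k = p + (1 − p)·(1 − L)·r
- Rate if only unknown statuses are dropped = k / (1 − u)

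**At 30% loss.**

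- True: 0.80 + 0.20·0.25 = 85%; 0.60 + 0.40·0.25 = 70%; difference 15 points.
- Unresolved: 0.20·0.30 = 6%; 0.40·0.30 = 12%.
- Known CT: 0.80 + 0.20·0.70·0.25 = 83.5%; 0.60 + 0.40·0.70·0.25 = 67.0%.
- Extreme bounds: 83.5 − (67.0 + 12) = 4.5; (83.5 + 6) − 67.0 = 22.5 points.
- All unknown counted as no CT: 83.5 − 67.0 = 16.5 points. All counted as CT: 89.5 − 79.0 = 10.5 points.
- Only unknown statuses dropped: 83.5/94 = 88.8%; 67.0/88 = 76.1%; difference 12.7 points.
- Every lost patient dropped, under random loss: 15 points, but known ED-visit CTs are thrown away.

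**At 10% loss.** Unresolved 2% and 4%; known CT 84.5% and 69.0%. Bounds: 84.5 − 73.0 = 11.5 and 86.5 − 69.0 = 17.5 points. Only unknown statuses dropped: 84.5/98 − 69.0/96 = 86.2% − 71.9% = 14.3 points.

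**Range over the assumed later-CT rate**, r from 0 to 30%, 100 per arm:

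| Loss | True difference | Lower bound | Upper bound | p at lower bound |
|---|---|---|---|---|
| 30% | 20.0 to 14.0 | 8.0 to 3.8 | 26.0 to 21.8 | 0.19 to 0.48 |
| 10% | 20.0 to 14.0 | 16.0 to 10.6 | 22.0 to 16.6 | 0.012 to 0.061 |

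At 30% loss the lower bound never reaches 0.047. At 10% loss it does for r of 0, 10% and 20%, but not for 30%.

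**The case against.** The other side has several good points.

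- **Complete-case analysis is not stated.** A reader might infer that the plan commits to it. It does not; this is the default of the named tests. A separate analysis plan is not shown and may say more. The criticism still stands, because it concerns what the article does state under its own missing-data item.
- **Doubling is a hypothesis.** A reader might infer that the aid itself doubles the share of patients whose status depends on follow-up. The 20% and 40% come from the planning rates, and Sample size {14} gives them no time window. If they describe 60-day CT, the split does not follow.
- **Doubling is confined to one measure.** It applies to any CT within 60 days. Dose, revisits and procedures depend on follow-up for every patient in both arms, so it does not extend to them.
- **30% is a threshold, not a forecast.** It is a feasibility limit applied after 50 participants. The design allows for 10% loss, where the bounds are much tighter.
- **Losing contact is not the same as an unknown CT status.** Chart review, outside-record authorization and contact attempts up to 16 weeks will resolve some cases. They reduce the gap but are not an analysis method, and the record search for unreached patients is stated for HRDwC only.
- **Bias towards a benefit is not shown.** The extreme bounds require opposite behaviour in the two arms. Dropping only the unknown statuses shrinks the effect, and counting them as unscanned enlarges it. Neither the size nor the direction is fixed until a rule is chosen.

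**Conclusion.** The point holds for the 60-day components of the radiation outcome. The stated approach is inadequate for a primary outcome that needs follow-up. On the planning rates read as ED-visit CT, with an assumed 25% later-CT rate, up to 6% and 12% of statuses are unresolved at 30% loss. A true 15-point difference could then lie between 4.5 and 22.5 points. At the 10% loss used for the sample size, the figures are 2% and 4%, and 11.5 to 17.5 points. Informative loss is not needed for the choice of rule to matter: dropping only unknown statuses gives 12.7 points under random loss at 30%.

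These are limits before record recovery, not expected errors. CT at the ED visit and the day-0 knowledge test do not depend on follow-up and are untouched.

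**What to change.** Replace the sentence in {20c} with a method for the 60-day outcomes:

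1. Keep every randomised patient in the intention-to-treat population, with ED-visit CT always counted as known. The plan's post-randomisation exclusions are a separate matter.
2. For patients not reached, apply the hospital-record search in {18b} to CT and dose as well as HRDwC.
3. Impute the values still unknown, by arm, using day-0 CT, stone history and available record data.
4. Add a tipping-point analysis that varies the CT rate among unresolved patients, and report complete-case results alongside.

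The cost is wording, some analysis time and a somewhat wider chart search. The main 60-day estimate would rest on a missing-at-random assumption, which the tipping-point analysis tests. If few statuses remain unknown after the search, the imputation will change little and the tipping-point result will show that.
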